## Abstract

**Background:**

As psychotherapy involves at least two individuals, it is essential to include the interaction perspective research. During interaction, synchrony, i.e., the occurrence of simultaneous responses, can be observed at the physiological, neural, and behavioral level. Physiological responses include heart rate and electrodermal activity; neural markers can be measured using electroencephalogram. Emotionally arousing stimuli are allocated more attentional resources (motivated attention), which is reflected in physiological activation and brain potentials. Here we present a protocol for a pilot study implementing a new research methodology, and replication of the motivated attention to emotion effect in in dyads. There is evidence that higher synchrony is associated with more positive (therapeutic) relationships. Thus, the secondary outcome will be the association between physiological and neural synchrony and subjective ratings.

**Methods and design:**

Individuals (18−30 years) will participate in same-sex pairs in two experiments. In the first experiment (triadic interaction), both participants attentively watch unpleasant, neutral and pleasant pictures, and read/listen to standardized scripts (unpleasant, neutral, and pleasant, respectively) for the imagination task. In the second experiment, participants will read out three scripts (unpleasant, neutral, pleasant) to each other, followed by a joint imagination period. Stimuli will be presented in counterbalanced orders. After each picture and imagination, participants rate their subjective arousal and valence. In the beginning and in the end of the procedure, dyads rate their relationship, sympathy, and bonds (Working Alliance Inventory subscale). Heart rate, electrodermal activity and electroencephalogram will be continuously measured during both experiments using portable devices (EcgMove4 and EdaMove4, nine-channel B-Alert X-Series mobile-wireless EEG). Synchrony analyses will include the dual electroencephalography analysis pipeline, correlational analyses and Actor–Partner Interdependence Models.

**Discussion:**

The present study protocol provides an experimental approach to investigate interpersonal synchrony during emotion processing, allowing for the establishment of research methods in a pilot study, which can later be translated into real-life psychotherapy research. In the future, fundamental understanding of such mechanisms in dyadic interactions is essential in order to promote therapeutic relationships, and thus, treatment effectiveness and efficiency.

## 1. Introduction

To date, a main focus of psychotherapy research has been on randomized-controlled trials and meta-analyses to investigate the effectiveness of specific psychotherapy procedures and methods. However, robust data on predictors of response, and mediators of change are lacking, leaving the specific mechanisms of action of psychotherapy largely unclear (1, 2). A thorough understanding of the mechanisms of action and its biopsychosocial determinants allows for the identification of person characteristics that contribute to the effectiveness and efficiency of a specific psychotherapeutic intervention [including the neuroscience-based approach; e.g., (3)].

Since psychotherapy involves at least two persons, understanding the interaction between patient and therapist (e.g., relationship, synchrony) is likewise important to advance psychotherapy research. The interaction can be described as triadic, where therapist and patient focus on the same object (e.g., a work sheet or a phobic stimulus), and dyadic, which is the face-to-face interaction between therapist and patient (4). Synchrony refers to the occurrence of two or more people’s responses at the same time (literally); the notion of simultaneity, or similar expression, which can be more or less pronounced (4). For example, synchrony can be observed in body movements (5), voice tone (6), and physiological responses [for reviews, see Koole et al. and Mende et al. (7, 8)]. Physiological responses in synchrony research include heart rate (4, 9), skin conductance (10, 11), and brain activity (12). Brain activity of two or more people can be measured simultaneously using hyperscanning methods [e.g., (13)]. For hyperscanning, broader research from the field of developmental psychology on parent-child interactions exists [for reviews, see (14, 15)], but methods might translate well into psychotherapy research. For example, using functional near-infrared spectroscopy (fNIRS), synchronous brain activity has been observed in therapist-patient interactions, and synchrony was especially pronounced for experienced therapists, which was associated with better working alliance ratings (16, 17). Furthermore, neural synchronization has been found to predict learning outcomes in teaching contexts [for meta-analysis, see Zhang et al. (18)], leading to the assumption that synchrony might also play a crucial role in new (inhibitory) learning essential to psychotherapy success (19). However, data on hyperscanning in psychotherapy is still a white spot on the research agenda.

Preliminary research found that positive relationships (e.g., a good therapeutic alliance/bond as a prerequisite for psychotherapy) go along with higher synchrony between individuals (7, 20). Although positive correlations between therapeutic alliance and therapy outcomes are modest, they are a robust finding (21). Accordingly, interactional subjective and (neuro-) physiological data should be integrated into the holistic view of mechanism-based personalized psychotherapy research.

The aim of the present study is to implement the measurement methodology and analysis of interpersonal synchrony using paradigms for emotion induction already established in individual settings. These allow for the simulation of emotional and neutral interactions, as they may also occur in psychotherapy, under laboratory-controlled, experimental conditions and in healthy students.

Emotions can be induced *via* various stimuli. Standardized picture material [International Affective Picture System, IAPS; e.g., (22–24)] and scripts for mental imagery [e.g., (25–29)] are particularly suitable. In contrast to neutral information, emotional content is allocated more attentional resources, and, consequently, more in-depth processing [motivated attention; (30)]. These processes can be investigated using neural (electroencephalogram; EEG) and peripheral physiological correlates, e.g., electrocardiogram (ECG, including heart rate, heart rate variability) and electrodermal activity (EDA).

During picture viewing, a triphasic pattern of heart rate response is usually observed, including (1) initial deceleration (orienting response), (2) acceleration, and (3) secondary deceleration (30, 31). The present pilot study focuses on the first two observations. Unpleasant (and, less consistently, high arousing, in contrast to low arousing pleasant) pictures have been found to evoke more pronounced initial HR deceleration, whereas pleasant pictures provoked higher acceleration relative to unpleasant [neutral pictures ranging in between; (30, 32)]. In line with these findings, evidence from appetitive and aversive conditioning suggest, that initial bradycardia might be rather valence-independent, indicating stimulus novelty or significance (33, 34).

Viewing of emotionally arousing, relative to neutral pictures has been associated with higher skin conductance level (SCL), pointing to higher sympathetic arousal (29, 30, 32). In the EEG, and especially in event-related potentials (ERPs), elevated Late Positive Potentials (LPPs) for emotionally arousing, relative to neutral pictures, have been observed over centro-parietal electrodes, starting at about 400 ms post-stimulus onset and lasting for several 100 ms, likewise indicating motivated attention (23, 24, 35). Preceding the LPP, the early posterior negativity (EPN, 150−350 ms post-stimulus onset) is also reliably enhanced for emotionally arousing, relative to neutral stimuli (36).

Similar reaction patterns during picture viewing and imagery have been observed for heart rate and skin conductance [(37, 38); for summary, see Ji et al. (39)]. In contrast, during imagery, the LPP emotion effect might emerge over more posterior electrodes, compared to picture viewing (40). However, there are conflicting LPP results, and research on ERPs of emotional imagery is still sparse (40, 41).

## 2. Methods and analysis

### 2.1. Participants

Inclusion criteria for participation in the intended study will be German language (level B2 or higher), student status (University of Greifswald), and age between 18 and 30 years. Females will be required to use oral hormonal contraceptives to exclude menstrual cycle influences on emotion processing [e.g., (42, 43)].

Exclusion criteria will be non-Caucasian, current or past mental or neurological disorder, as well as acute illness and/or medication. Participants will be required to have normal or corrected-to-normal vision and hearing. Participants will receive course credit for participation. For controllability, only same-sex pairs with heterosexual orientation will be included.

### 2.2. Stimulus materials

#### 2.2.1. Picture stimuli

Sixty pictures (20 unpleasant, 20 neutral, 20 pleasant) have been selected from the International Affective Picture System [IAPS (22) and the EmoPics (44)] according to their normative valence (unpleasant: *M* = 2.4, SD = 0.63; neutral: *M* = 5.22, SD = 0.41; pleasant: *M* = 7.11, SD = 0.63; all *p*s < 0.001) and arousal ratings (unpleasant: *M* = 6.13, SD = 0.6; neutral: *M* = 2.87, SD = 0.33; pleasant: *M* = 5.97, SD = 0.79; unpleasant = pleasant >neutral, *p* < 0.001). Semantic categories include attack, mutilation, accident/disgust for unpleasant, neutral objects and people, and nature/buildings for neutral, and cute animals, babies/people, erotica, and sports/adventure for pleasant scenes, respectively, (see Supplementary material 1).

#### 2.2.2. Imagination scripts

Nine scripts (3 unpleasant, 3 neutral, 3 pleasant) have been selected from the Affective Norms for English Text [ANET; (26)], German translation (see Supplementary material 1).

### 2.3. Procedure

After arrival to the lab, participants will provide written informed consent to the study protocol approved by the ethics committee of the University Medicine Greifswald and sensors will be attached according the manufacturers’ manuals. If necessary, participants will get to know each other introducing themselves briefly (first name, age). Then, they will fill in the modified Working Alliance Inventory [WAI-SR, German; (45)] bonds-subscale (Items 3, 5, 7, 9, see Supplementary material 2) and rate their relationship and sympathy on a nine-point Likert scale (1 = “completely unknown/do not like at all” to 9 = “very well-known/like very much”; ratings are never revealed to the partner and participants have to sign a declaration of confidentiality). Data acquisition will take place in a sound-attenuated, dimly lit cabin. Following a 10 min baseline (rest, black screen), experiments A and B will be conducted in counterbalanced order. Finally, individuals will fill in the bonds-subscale (WAI-SR) and will be told the objectives of the experiment. Apart from the experimental interaction procedure, participants will be instructed neither to engage in conversation, nor to communicate *via* gesture or mimics.

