### 2.4. Data acquisition and pre-processing

Subjective rating data will be registered *via* Presentation Software (Version 23.1; Neurobehavioral Systems Inc., Berkeley, CA, USA) and logfiles will be further processed using IBM SPSS Statistics Version 29.0 (IBM Corp., Armonk, NY, USA) SPSS (Version 29.0, Armonk, NY, USA). ECG and EDA will be measured using EcgMove4^1^ and EdaMove4^2^ (movisens GmbH, Karlsruhe, Germany), respectively. For the continuous single channel ECG signal (sampling rate of 1024 Hz), a dry electrode chest belt associated with the EcgMove4 system will be used. An EDA sensor associated with the EdaMove4 system will be used to continuously measure EDA (sampling rate of 32 Hz) using a wrist-band and two disposable electrodes are attached to the hypothenar. The built-in activity sensor will register acceleration in three-dimension, angular rate (gyroscope), air pressure and temperature.

Raw sensor data will be read out, visualized and saved using the free and open software UnisensViewer (movisens GmbH, Karlsruhe, Germany), and will then be exported into MATLAB (The MathWorks Inc., Natick, MA, USA; raw ECG data and skin conductance level, SCL, for EDA). For subsequent analyses, ECG raw data will be digitally sampled down at 400 Hz and corrected for artifacts using the Autonomic Nervous System Laboratory [ANSLAB; (47)]. The software automatically detects R-wave-triggers to marker single heart beats; misplaced R-wave-triggers will be checked and corrected whenever they occur. The data will be converted into heart rate in beats per minute for every half-second bin of the sampling period and further analyzed with SPSS. The built-in activity sensor data (acceleration in three-dimension, angular rate, and temperature) will be analyzed together with EDA because of the potential influence of these variables on EDA. To control for possible effects of differences in the overall skin conductance level (SCL) on phasic SCL changes, SCL will be range-corrected per subject using all available data points during all experimental tasks. Both, SCL and heart rate (computed by converting RR-intervals into beats per minute) will be reduced into 1 sbins for synchrony analyses.

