### 2.5. Data analysis

Questionnaires and behavioral data will be imported from Presentation into SPSS (Version 29; IBM, Armonk, NY, USA).

To investigate the emotion effect, ANOVAs involving the within-subjects factor emotion (unpleasant vs. neutral vs. pleasant) will be conducted. Involving the additional between-subjects factor partner (partner 1 vs. partner 2), requires a total sample size of *N* = 42 to reveal medium size effects [obtained with G*Power, Version 3.1; alpha error probability = 0.05; power = 0.95; partial η^2^ = 0.06; (48)]. For theses analyses, heart rate will be extracted between 1 s prior to picture onset (baseline) and picture offset (3 s). Skin conductance change will be scored as the maximum response (between 1 and 3 s after picture onset). During the imagery reading/listening task, autonomic reactions will be determined by subtracting amplitudes in the first second prior to script presentation from response averages during the 15 s read and 12 s imagery periods.

For ERP analyses, data will be segmented starting 100 ms before (baseline) and 1.200 ms after stimulus onset for each sensor and means ERPs for each emotion category and subject are calculated [see (23)]. Time-windows and sensor sites for EPN and LPP analyses will be chosen following visual and statistical data inspection of individual averages for each valence category, using Randomization Graphical User interface toolbox (49).

For the picture viewing paradigm, each valence block is expected to last approximately 15 min, depending on the speed of the self-paced SAM-ratings. In the imagination task, a run including the three valences will take about 3.5 min, again depending on individual SAM-rating durations.

Thus, for synchrony analyses, signal streams will be synchronized for both subjects and then transformed in interval data. These time rows will be imported into SPSS for further analysis.

For this purpose, EEG data will be exported as MATLAB file (synchronized data for both individuals) and transformed *via* script into Brain Vision Analyzer (Version 2.2.2; Brain Vision, Morrisville, NC, USA) format to allow for artifact correction, filtering and further processing with dual electroencephalography (EEG) analysis pipeline [DEEP; (50)].

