Moreover, correlational analyses and Actor–Partner Interdependence Models (APIM) are planned to analyze the influence of synchrony on subjective and interpersonal ratings (51, 52). Separate APIMs are planned for each measure (Heart rate, skin conductance, EEG) in the different tasks (independent variables) and subjective bonds-rating after the experiments (dependent variables).

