### 2.6. Outcome and hypotheses

Primary research question is the successful implementation of the picture viewing and imagination paradigms from an individual setting into the two-person interaction, aiming at the replication of the enhanced attention to emotion effect [motivated attention; (30)] in subjective ratings (SAM), physiological (ECG, EDA) and neuronal (EEG) markers, and the development and testing of new data analysis strategies. Secondary outcome will be the influence of synchrony in physiological and neuronal activity during picture viewing and imagination on subjective emotion experience and interpersonal ratings after the experiment (WAI-SR).

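### No stated analysis uses the 10 min resting baseline, so the synchrony–rating models cannot tell task-related coupling from coupling a pair already shows at rest

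*Protocol article*

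**What the plan says.** The protocol article, section 2.3, has sensors attached on arrival. The partners then rate bond, relationship and sympathy. After that: "Following a 10 min baseline (rest, black screen), experiments A and B will be conducted in counterbalanced order". The rest is labelled a baseline and is not mentioned again.

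The stated references and predictors are these:

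- Heart rate during pictures (2.5): "heart rate will be extracted between 1 s prior to picture onset (baseline) and picture offset (3 s".
- Autonomic responses during imagery (2.5): "subtracting amplitudes in the first second prior to script presentation from response averages".
- ERPs (2.5): "data will be segmented starting 100 ms before (baseline) and 1.200 ms after stimulus onset".
- Skin conductance (2.4): "SCL will be range-corrected per subject using all available data points during all experimental tasks".
- Models for the bond rating (2.5): "Separate APIMs are planned for each measure (Heart rate, skin conductance, EEG) in the different tasks (independent variables".

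The secondary outcome in 2.6 is the "influence of synchrony in physiological and neuronal activity during picture viewing and imagination" on emotional experience and interpersonal ratings. Section 2.6.2 applies this to agreement in SAM ratings and 2.6.3 to the bond rating after the experiment.

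On recording, the abstract says: "Heart rate, electrodermal activity and electroencephalogram will be continuously measured during both experiments using portable devices". It does not mention the rest.

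**The concern.** A pair's synchrony during a task may have two parts: coupling evoked by the shared stimulus or interaction, and coupling the pair would show with no stimulus at all. The second part belongs to the pair, so a chance-level reference from re-paired strangers would not remove it. The rest is the one lengthy stimulus-free period in the design that could show how large it is.

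If pairs with more resting coupling also rate each other higher, a model with task synchrony alone will show an association even when the emotion tasks add nothing. The same holds for agreement in SAM ratings. At stake is how the secondary result is read: as something arising during emotion processing, or as a standing feature of the pair.

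**Working it through.** **1. Where the rest could enter**

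| Quantity | Stated reference or input | Uses the 10 min rest? |
|---|---|---|
| Heart rate, pictures | 1 s before onset | No |
| Autonomic response, imagery | 1 s before script | No |
| ERP | 100 ms before onset | No |
| Skin conductance range correction | Task data | No |
| Synchrony predictor | Each measure in each task | No rest term named |

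**2. The plan's own figure.** Section 2.5 gives N = 42 for partial η² = 0.06, alpha 0.05 and power 0.95.

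- f² = 0.06/0.94 = 0.0638, so f = 0.2526.
- With three emotions, two groups, and assumed defaults of correlation 0.5 and no sphericity correction (neither is stated), λ = f²·N·m/(1 − ρ) = 0.0638 × 42 × 3/0.5 ≈ 16.1.
- With 2 and 80 degrees of freedom, power is 0.951. N = 40 gives 0.940.

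So 42 reproduces. It sizes the emotion ANOVA and no synchrony test. It supplies 42/2 = 21 pairs.

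**3. Resting coupling alone relates to bond.** Let S = √s·R + √(1 − s)·T, where S is task synchrony, R resting coupling, T the task-specific part and s the resting share. Assume bond correlates 0.5 with R and 0 with T, and use one bond value per pair (a simplification of the APIM). Then corr(S, bond) = 0.5·√s.

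- s = 0.3/0.5/0.7 gives r = 0.27/0.35/0.42.
- Approximate rejection rate: Φ(atanh(r)·√18 − 1.96) + Φ(−atanh(r)·√18 − 1.96) = 0.22/0.35/0.47.
- Simulated t-tests with 21 pairs give about 22/35/49%.

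These shares imply rest–task correlations of √s = 0.55/0.71/0.84. If the correlations are instead 0.3/0.5/0.7 (shares 9/25/49%), r = 0.15/0.25/0.35 and the rate is 0.10/0.19/0.34.

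**4. Same scenario, resting synchrony as covariate** (shares 30/50/70%)

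| Reliability of resting synchrony | Rejection rate |
|---|---|
| 1.0 | 5–6% |
| 0.8 | about 6–10% |
| 0.6 | about 8/13/18% |

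**5. Power when there is something to find** (r = 0.5, shares 30/50/70%, reliability 0.8)

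| Bond depends on | Unadjusted | Adjusted |
|---|---|---|
| Task-specific part only | 49/35/23% | 60/55/45% |
| Total task synchrony | about 67% throughout | about 53/45/34% |

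**6. Adjusting for the starting bond instead.** If prior liking drives resting coupling, adjusting for the pre-experiment rating brings the 22/35/49% down to about 5% when that rating is perfectly measured, and to about 6/7/9% at reliability 0.8. If resting coupling has other sources, the pre-rating carries no information about them and cannot remove their share.

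**The case against.** The strongest reply is that 2.6.3 names a time window, not an increment over rest. The introduction and discussion motivate it by positive relationships going along with higher synchrony in general, so a pair's stable coupling may be part of what is meant. On that reading the unadjusted model answers the question, and adjustment costs power. This stands: the total-synchrony estimate should be kept as a result in its own right.

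Second, the article condenses a fuller protocol, and model covariates are often left to that. This limits the weight of the point. It does not remove it, because the article spells out a reference window for each response measure and names the predictors and outcome of the bond models, and the period it labels a baseline appears in none of them.

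Third, the rest may not be a perfect match. Recording and seating during it are not stated, and in Experiment B the partners face each other. That is a reason to state these facts and to read the adjusted estimate with care.

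A reader might also infer that leaving out the rest generally costs the synchrony tests power. Step 5 shows that the direction depends on which part of synchrony matters, and the article does not settle that. Nor can one say that adjusting for the starting bond fails. It works where prior liking is the source.

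**Conclusion.** The point holds for the secondary outcome. As described, the models cannot separate task-related coupling from coupling already present at rest, so an association could be credited to the emotion tasks wrongly. If resting coupling correlates 0.5 with bond and the task adds nothing, the unadjusted test with 21 pairs rejects in about 22/35/49% at resting shares of 30/50/70%, or about 10/19/34% at rest–task correlations of 0.3/0.5/0.7. With resting synchrony as covariate at reliability 0.8, the first set falls to about 6–10%. All shares, correlations and reliabilities are assumptions.

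A reader might go further and conclude that resting coupling is in fact being credited to the tasks. The article reports no resting coupling, so it supports only that this could happen. That the rest is recorded, and recorded jointly, is inferred from its label and from the sensors already being in place. The primary emotion effect is a within-subject contrast with its own pre-stimulus reference and is unaffected.

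**What to change.** In section 2.5:

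1. Confirm that heart rate, skin conductance and EEG are recorded for both partners during the 10 min rest, and state how they are seated.
2. Compute each synchrony index on the rest with the same bins and window length as in the tasks.
3. For every model under 2.6.2 and 2.6.3, report the planned estimate (total synchrony during the task) next to one with the pair's resting synchrony as covariate.
4. Describe an association as specific to the emotion tasks, beyond resting coupling, only with support from the adjusted estimate. The total-synchrony result stands as its own estimate.

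If signals are recorded during the rest, the cost is analysis work only. The adjusted model loses one degree of freedom and is less precise when rest and task synchrony are strongly correlated. An unreliable resting index leaves part of the problem in place (step 4 of the working).
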